### Statistical analysis

2.6

SPSS 18.0 (SPSS, lnc., Chicago, IL), Stata10.0 (StataCorp, College Station, Texas), and other statistical software are used for data analysis with a 2-sided significance level of 0.05, the point estimate, and 95% confidence interval. If the data obey the normal distribution and the variance is homogeneous, data are expressed as the number of cases (n) and the mean ± standard deviation (SD). Before and after treatment at multiple time points, measurement data using repeated measurement of variance analysis and multiple variance analysis are expressed as median (M), minimum (min), and maximum (max). The Kruskal–Wallis H test is used to compare the data between the 2 groups. The numerical variables are measured at multiple time points before and after treatment, and the generalized estimating equations or mixed effect models are used for the classification and sorting variables. If the analysis index is disordered using χ^2^ test, the analysis index is ordered with rank sum test, the 2-way ordered attribute of different data using linear χ^2^ test, and rank sum test. The survival rate is calculated by Kaplan–Meier method (K-M method), and the survival curve is drawn. Multivariate data are analyzed using multiple linear regression analysis, COX regression analysis, trend testing, and so on.

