### Sample size

2.2

Considering the results of the study at MD Anderson Cancer Center in foreign countries^[15]^ showed that the 3-year survival rate of TNBC patients was significantly shorter than that of non-TNBC patients (74% vs 89%, *P* < .01), as well as the lost rate of 20%, the sample size (N) is calculated by the following formula: 
[figure not shown]

*P*_0_ means the recurrence and metastasis rate of the nonexposed group; *P*_1_ represents the recurrence and metastasis rate of the TCM exposure group, *P*_1_ = RR × *P*_0_, where RR is the relative risk caused by exposure factors.

This study assumes that α = 0.05 and β = 0.10. According to the related study, the rate of recurrence and metastasis was 12% in the TCM group and 33.33% in the western medicine treatment group, respectively. The relative risk (RR) of TCM intervention was that RR = 12%/33.33% = 0.36. Domestic and foreign data showed that the 2-year recurrence and metastasis rate of TNBC patients was 17%, so *P*_0_ = .17, *P*_1_ = RR × *P*_0_ = 0.06.

Substituting the formula, the calculated amount of each group is as follows: 

Considering the 20% of drop rate, the confinement factor in different hospitals increased by 10% of the sample size, that is, at least 249 (N ≥ 249) cases should be observed in each group. Then, combined with the study period and the target population distribution of the study unit, 310 cases should be included in the Chinese medicine and Western medicine groups, respectively, in this study.

Before the research, investigators are responsible for the introduction the clinical research related matters and the records of the baseline data, then all participants sign the informed consent form. Patients in the TCM exposure group take Chinese medicine (San Yin Decoction) as well as original Western medicine, while patients in the nonexposed group only receive Western medicine treatment. The study will be performed during 2 years, and all results are recorded according to the Case Report Form (CRF).

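### Repeated numerical secondary outcomes are assigned to repeated-measures ANOVA and MANOVA, which in their standard form keep only patients complete at every visit, although the plan expects 20% loss

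*Protocol article*

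**What the plan says.** Section 2.6 (Statistical analysis) sets the method for numerical data collected before and after treatment at multiple time points: "measurement data using repeated measurement of variance analysis and multiple variance analysis". Two sentences later it turns to other variable types: "the generalized estimating equations or mixed effect models are used for the classification and sorting variables".

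Section 2.3.2 (Secondary outcomes) has the symptom score, KPS, QLQ-BR23, tumour markers and immune measures assessed every 3 months. Sections 2.1 and 2.2 set a study period of 2 years. The Abstract gives a different schedule: baseline and six later assessments, expressed in weeks.

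The sample-size text (section 2.2) mentions loss twice, the second time in the inflation step: "Considering the 20% of drop rate, the confinement factor in different hospitals increased by 10% of the sample size". The cohorts are formed by whether patients take TCM (section 2.1), not by randomisation.

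**The concern.** A patient who is seen for most of the study and then lost has a partly observed series. MANOVA, and repeated-measures ANOVA run in the usual one-row-per-patient layout (the SPSS GLM procedure), remove such a patient entirely, earlier visits included. The plan expects a fifth of patients to be lost, so this is the ordinary case.

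Two things are at stake. One is precision, because observed data are thrown away. The other is validity. A completers-only comparison needs dropout to be unrelated to the outcome, or at least to act alike in both cohorts. Nothing in a non-randomised design ensures that. Quality of life is named in the study's purpose in the Abstract, so these outcomes are not peripheral even though they are secondary.

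The plan already names a method that uses partial series, but for other variable types.

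**Working it through.** **1. Is the 20% loss a real planning input?** The formula is a figure that is not shown, so I tried the standard two-proportion form with the inputs of section 2.2: P0 = 0.17, RR = 0.36, P1 = 0.36 × 0.17 = 0.0612, two-sided α = 0.05, β = 0.10.

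- p̄ = (0.17 + 0.0612)/2 = 0.1156
- n = (1.960 + 1.282)² × 2 × 0.1156 × 0.8844 / (0.17 − 0.0612)² ≈ 181.5 per group
- 181/(1 − 0.20) × 1.10 = 248.9, so 249

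A slightly different pooled variant gives 180, and 180/0.80 × 1.10 = 247.5, so 248. The stated minimum of 249 per group is therefore reproduced to within rounding, and the 20% is built into it. The planned size is 310 per group, 620 in all.

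**2. Complete cases from the stated loss alone.** 620 × (1 − 0.20) = 496, or 248 of 310 per group; 620 − 496 = 124 patients are excluded. No further assumption is needed except that each lost patient misses at least one scheduled visit. If deaths are not counted within the 20%, the number is lower.

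**3. Adding intermittent missed visits (assumption).** With K follow-up visits and a miss rate m per visit, independent across visits:

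complete cases = 620 × 0.80 × (1 − m)^K

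K = 6 follows the Abstract. K = 24/3 = 8 follows the 3-monthly schedule over 2 years.

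| m | K = 6 | K = 8 |
|---|---|---|
| 1% | 620 × 0.7532 = 467 | 620 × 0.7382 = 458 |
| 5% | 620 × 0.5881 = 365 | 620 × 0.5307 = 329 |

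The documents give no per-visit miss rate. Missed visits tend to cluster within patients, which would leave more complete cases than independence implies.

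**4. Bias.** An illustrative simulation assumed 310 per group, 9 time points, autoregressive correlation 0.8, about 20% dropout, no true difference and 300 repetitions. It gave these errors in the final-visit difference (Monte Carlo standard error about 0.005 SD):

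| Dropout mechanism | Completers only | Likelihood on all available data |
|---|---|---|
| Unrelated to outcome, both groups | −0.012 SD | −0.011 SD |
| Depends on previous value, both groups alike | 0.003 SD | 0.007 SD |
| Depends on previous value, one group only | −0.069 SD | 0.011 SD |

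Material bias appears only when outcome-related dropout differs between groups, and there the all-data analysis largely removes it.

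**The case against.** **The software does not always delete.** The plan names SPSS, Stata and other packages without fixing a procedure. A long-format univariate ANOVA, as in Stata, can keep partial records. This stands: a reader might infer that every ANOVA route drops every patient with a missed visit, and the documents do not support that. Deletion holds for MANOVA, which the plan also names, and for the wide-format ANOVA.

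**Missing-data rules may sit in an unseen analysis plan.** They may, and their absence from a condensed article is not the point here. The point is the method the article does choose.

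**The wording is garbled.** The sentence naming mixed models opens with numerical variables, and the ANOVA sentence ends with medians and ranges as summaries. Its literal assignment of mixed models is nevertheless to categorical and ordered variables. If it were read to include numerical ones, section 2.6 would give two methods for the same data and no rule for choosing. Either way the text needs the same edit.

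**Some outcomes are categorised.** Section 2.3.2 rates TCM symptom and KPS efficacy in three levels. This stands: those two belong here only where their scores are analysed as numbers. QLQ-BR23 scores, tumour markers and immune measures remain.

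**Differential dropout is not shown.** A reader might infer that patients leave the series at recurrence, so that the assumed 17% and 6% translate into unequal dropout. The documents do not say this. Those figures are recurrence and metastasis rates, no section stops assessments at recurrence, and the text before Table 4 has all participants followed by telephone and outpatient visits. Unequal dropout is plausible in non-randomised cohorts, but it remains a condition and not a finding.

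**Conclusion.** The point holds for numerical secondary outcomes. As specified, and in the standard implementation, the analysis would use at most 496 of 620 patients if the planned 20% loss occurs. With an assumed 1 to 5% of visits also missed independently over 6 to 8 visits, about 467 to 329 remain. A larger headline loss can be produced by assuming higher miss rates, but nothing in the documents supports a particular rate.

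The loss of precision follows from the deletion itself. Bias is conditional on outcome-related dropout differing between cohorts; in the illustration it was about 0.07 SD. Progression-free and overall survival are unaffected, since the plan uses Kaplan–Meier and Cox methods for survival. This is a change that should be made, but it does not threaten the primary analysis.

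**What to change.** In section 2.6, replace repeated-measures ANOVA and MANOVA for numerical outcomes with a linear mixed model fitted to all available visits. Include cohort, visit, cohort-by-visit, baseline value and hospital as terms. Transform skewed tumour markers before fitting. Report the cohort difference with its 95% confidence interval. State which of the symptom and KPS analyses use scores and which use the three-level categories, and reconcile the Abstract's visit schedule with section 2.3.2 so that the number of repeated measures is fixed.

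The cost is a wording change and slightly more analysis work, with no new data or patients; the plan already names this class of model. Every patient with a baseline and at least one follow-up value can then contribute. The model assumes data missing at random given what was observed. It does not by itself settle how values after death are to be understood, and it does not remove confounding between non-randomised cohorts.

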### Adverse events

2.7

During the entire study period, AEs will be reported and recorded in the participants’ CRF table. The severity of AEs will be graded as mild, moderate and severe, and their relationship between the study groups will also be assessed by clinical judgement. If an AE requiring hospitalization or causing a medically critical situation occurs, the event will be recorded as a severe adverse event (SAE). All SAEs will be reported to the investigator of the attending hospital and the IRB of reference within 24 h after the information has been collected. AEs that cannot deny a relationship to the study must be followed until the AEs have been resolved. Whenever AEs progress to the level of SAEs, the events must also be reported according to the above protocol. At the time of the study result submission, AEs and their relationship to the study will be documented in a table and submitted.

## Discussion

3

TNBC has a huge population of patients in China; therefore, the effective measures for the prevention and treatment of BC have become the focus of many scholars.^[19]^ Although the current treatment options for BC is chemotherapy in China,^[20]^ TCM treatment has been considered to play an important role in the treatment for BC. In China, many postoperative TNBC patients receive TCM treatment and get good treatment effect. However, few systematic studies on TCM treatment for postoperative TNBC patients have been conducted, which may lead to the failure of TCM treatment due to lacking of treatment norms and compliance, losing the confidence to overcome the disease.

On the basis of the development of evidence-based medicine and the importance of comprehensive treatment of BC,^[21]^ Cancer Treatment Model, including Chinese medicine, surgery, radiotherapy and chemotherapy, endocrine therapy and biological immunization, and other standardized, individualized comprehensive treatment has become the current international trend of cancer treatment, especially BC treatment. This study will verify this model and introduce evidence-based medicine into the field of research, which will be beneficial to the objective evaluation of TCM syndrome differentiation in the treatment of refractory BC and promote the TCM treatment globalization.

After the completion of this study, the database of TNBC patients in China will be established to conduct long-term dynamic follow-up, health education, and medication guidance for patients, as well as change the 1-way and imperative diagnosis, and treatment process in the past. A dynamic interactive process can be established by basic and clinical researchers, which may lead to an active medical treatment model.

We believe that this cohort study will not only prove the curative effect of TCM but also propose a more standardized and humane treatment plan for TNBC people, which will be beneficial to more and more patients through long-term inheritance.

## Trial status

4

The basic observational cohort clinical study has received governance approval and is registered at ClinicalTrials.gov (NCT03332368). The trial started recruitment in January 2017.
